According to the socio-ecological model, an individual’s behaviour is affected by and affects the social environment. Therefore, holistic interventions are more practical in addressing healthy ageing [29]. Environmental factors may have an essential role in the modulation of food and physical activity (PA) habits [30]. Food, such as availability and accessibility to supermarkets, grocery or convenience food stores, and restaurants [30], and PA, such as details on walkability, parkland use, access to PA facilities [30,31], and environmental features must be considered. The use of Geographic Information Systems (GIS) can provide a novel and better understanding of the available environmental features, contributing to the implementation of effective healthy ageing policies [29].

Therefore, our primary aim is to assess the effect of different SHD and MT interventions on the biochemical and metabolic profiles, nutritional statuses and adequacy, physical fitness, body composition and anthropometry, cognitive function, and quality of life of older adults through a quasi-experimental study. Additionally, as a secondary aim, we intend to characterise food and PA environmental features and study their potential role in the modulation of food and PA practices.

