### 2.2. Eligibility and Recruitment

This study included individuals (i) aged 65 years or older, (ii) living in the community, (iii) with independent mobility, (iv) with no past medical history of neuropsychiatric conditions (e.g., major depression or bipolar disease), and (v) with no musculoskeletal or cardiovascular disorders that contraindicate participation in moderate exercise and testing. The exclusion criteria included individuals engaged in regular moderate to vigorous exercise training and followed by a nutritionist.

Eligible participants received a complete explanation of the study’s purposes, risks, and procedures. Before data collection, the principal researcher obtained informed consent from interested participants. After the agreement, participants were assigned into a 3-month SHD, MT, combined SHD and MT (SHD + MT), or control group (CG). 

Participants were assessed at baseline and after 3 months of intervention. At baseline, sociodemographic and economic, lifestyle (e.g., tobacco use and habitual physical activity), and general clinical data were collected through a structured questionnaire. Possible changes in these data were assessed in post-intervention assessments. At these two time points, nutritional and food intake evaluations were obtained through multiple reliable tools [33,34,35]: the Mini Nutritional Assessment [36]; physical capacity assessments through the Senior Fitness Test [37] and handgrip strength; a whole-body Dual X-ray absorptiometry (QDR 4500/A, Hologic Explorer, version 12.4, Bedford, MA, USA); a Montreal Cognitive Assessment [38]; the Quality of Life for Old Module (WHOQOL-OLD) [39]; and accelerometry (ActiGraph GT9X Link, Manufacturing Technology, Inc., South Bend, IN, USA) were performed. 

Participants were only informed about which group they belonged to after baseline assessments. Well-trained and skilled researchers executed the same procedures during the two assessment periods.

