#### 2.6.3. Confounders

As possible confounders, we will control at baseline and after the intervention for (i) sociodemographic and economic status, (ii) clinical history, (iii) tobacco use, (iv) medication (collected through a structured questionnaire), and (v) daily physical activity, assessed through an accelerometry-based method (ActiGraph GT9X Link, Manufacturing Technology, Inc., South Bend, IN, USA). Participants were instructed to always wear the accelerometer for seven consecutive days attached to an elastic belt, except when sleeping or during water activities. Data were collected in 100 Hz epochs; valid data must include a minimum of 10 h on at least four days (with one weekend day). This data will be processed using Actilife™ software, version v6.13.4 (Actigraph LLC, Pensacola, FL, USA) and organised as sedentary, light, moderate, and vigorous physical activity.

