### 2.7. Statistical Analyses

Descriptive results will be expressed as median and inter-quartile range (IQR) or mean and standard deviation (SD), as appropriate, for continuous variables. Discrete variables will be presented as counts and percentages. The minimum threshold value for statistical significance used will be *p* ≤ 0.05.

The normality tests, histogram, and plot distribution will assess the normality of data distribution. Comparative analyses between participants and dropouts will be realised by *t*-test or Mann–Whitney U-test for continuous variables and Pearson-Chi Squared or Fisher exact test for categorical variables to determine whether attrition bias was observed. 

Potential differences among intervention groups in baseline measurements will be evaluated using a one-way Analysis of Variance (ANOVA) or correspondent non-parametric Kruskal-Wallis test. A Pearson Chi-squared or Fisher exact test will be used for between-group comparisons of categorical variables. 

Covariates (e.g., sociodemographic and economic characteristics; clinical history, such as the presence of comorbidities; and daily physical activity) were selected a priori and tested. The confounding variables will be entered as covariates in the ANOVA models. For each model, the contribution of all covariates will be tested separately; only the ones that change the magnitude of the association by at least 10% will be included in the final models. The fit of the models will be determined. Whenever necessary, we will use weighted samples to tackle the bias imposed by differential sampling probabilities.

A delta percentage will be calculated to assess the percentage of change between baseline and post-intervention assessments. An ANOVA or correspondent non-parametric test with repeated measures will be performed for differences in main effects and interactions for each dependent variable. When significant interactions are found, Bonferroni posthoc tests will determine the origin of the differences. Multivariable regression analyses will explore the associations between blood-based markers and metabolomics and the secondary outcomes.

Geographical information systems data will be collected. The associations of the primary and secondary outcomes with environmental features will be explored through generalised linear models to understand whether built environment food and PA features lead to statistically significant differences in participants’ dietary and exercise routines.

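### Section 2.6.3 allows adjustment for physical activity measured after the intervention, so the models need not estimate the total effect of the training arms

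*Protocol article*

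**What the plan says.** The Introduction sets the target: "our primary aim is to assess the effect of different SHD and MT interventions" on biochemical, metabolic and other outcomes.

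Section 2.6.3 then states "As possible confounders, we will control at baseline and after the intervention for" a list of five groups of variables. The last two are "iv) medication (collected through a structured questionnaire), and (v) daily physical activity, assessed through an accelerometry-based method". For the device, "Participants were instructed to always wear the accelerometer for seven consecutive days"; only sleep and water activities are exempt.

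Section 2.2 shows that the later values exist. Accelerometry is among the assessments made at both time points, and for the questionnaire data "Possible changes in these data were assessed in post-intervention assessments".

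Section 2.7 says what is done with these variables: "The confounding variables will be entered as covariates in the ANOVA models". It gives daily physical activity as one of its examples. On retention, "only the ones that change the magnitude of the association by at least 10% will be included in the final models". Neither section limits the covariates to values taken before the intervention.

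**The concern.** A confounder must not itself be a consequence of the intervention. Activity measured after three months of an exercise programme can be such a consequence. If it is entered as a covariate, the model compares arms as though their activity after the intervention had been equal, although changing activity is what the training arms are for. The group coefficient then describes only the part of the effect that does not run through measured activity, and not the total effect that the aim asks for.

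Two kinds of error follow. Where activity mediates the effect on a biomarker, the MT and SHD + MT estimates are typically attenuated. Where something unmeasured affects both later activity and the biomarker, conditioning on activity opens a further bias whose direction is not known in advance. A weak or null result for the training arms could then come partly from the model.

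**Working it through.** **Step 1. Can assignment change post-intervention activity?** Four statements in the protocol article, taken together, say that it can:
- The MT programme is three 50-minute sessions a week, 3 × 50 = 150 minutes (section 2.5.2).
- Controls are advised to keep their usual routines and are offered two low-intensity activity sessions (section 2.5.4).
- People already in regular moderate to vigorous training are excluded (section 2.2).
- The device is not taken off for exercise sessions (section 2.6.3).

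The Introduction also reports that exercise lowers LDL-C, CRP, insulin and glucose, all of which are among the primary biomarkers in section 2.6.1. For those markers, activity as a path from assignment to outcome is part of the trial's own rationale.

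**Step 2. What does adjustment estimate?** The plan gives no figure for this bias, so there is none to reproduce. Let T be assignment (MT against control), M post-intervention activity and Y a biomarker:
- M = aT + error
- Y = c′T + bM + error

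The total effect is c′ + ab. The coefficient of T adjusted for M is c′. The fraction removed is s = ab / (c′ + ab), the share of the effect that runs through activity.

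**Step 3. Illustration.** The document gives neither s nor the total effect. Assume a total of 0.80 SD, used only to set the scale (s does not depend on it), and s of 25% or 50%:
- s = 25%: 0.80 × 0.75 = 0.60, so 25% is removed.
- s = 50%: 0.80 × 0.50 = 0.40, so 50% is removed.

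A large-sample simulation (400,000 participants, a = 0.25, 0.5 and 0.8) gives 0.597 to 0.602 and 0.395 to 0.399. It confirms the algebra and is no evidence about the true s.

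**Step 4. Add an unmeasured common cause.** Let it act with coefficient 0.3 on both M and Y, with the variance of M within arm equal to 1. The adjusted coefficient becomes c′ − a × 0.3 × 0.3 = c′ − 0.09a.
- a = 0.25, s = 25%: 0.60 − 0.0225 = 0.5775, a loss of about 28%.
- a = 0.8, s = 50%: 0.40 − 0.072 = 0.328, a loss of about 59%.

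If the common cause acts with opposite signs on M and Y, the term becomes + 0.09a. With a = 0.8 and no mediation (s = 0), the adjusted value is 0.80 + 0.072 = 0.872, above the true total. The direction is therefore not fixed.

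**Step 5. Does the 10% rule help?** In the model of step 2, the relative change in the group effect on adding M is s itself. The rule drops a mediator that carries less than 10% of the effect and keeps one that carries 10% or more. It selects the variable in the cases where including it does most harm.

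**The case against.** The best defence is that control in section 2.6.3 means measurement. The subsection sits under outcome assessments, most of its text describes data collection, and section 2.2 uses similar two-time-point language for assessment alone. Section 2.7 never says that post-intervention values are entered. The reading is possible, but it does not fit well. The sentence names the variables as confounders to be controlled for, and section 2.7 makes confounders into covariates without a baseline limit. An analyst who follows the text could properly enter the later values. Nor is this a detail merely left to a fuller document: the article states a rule, and the rule as stated is wrong for its aim.

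A second defence is that a non-randomised study needs adjustment. It does, for values at baseline, and the fix keeps all of that.

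Several stronger conclusions are tempting but not supported:
- **That every primary biomarker is pulled towards zero.** Attenuation needs activity to respond to assignment, to affect that marker in the direction of the total effect, and to be retained. The list includes vitamin B12, sodium, phosphorus and osmolality, for which the document shows no such path.
- **That post-intervention activity is certain to be in the models.** Inclusion depends on the 10% rule.
- **That the 150 weekly minutes are certainly recorded.** The article does not say whether the second wear week overlaps the sessions. Activity outside the programme could still respond to assignment.
- **That medication and clinical status raise the problem to the same degree.** They might respond to a 12-week programme, but nothing in the document shows it.
- **That a particular loss of power follows.** Any such figure would only restate an assumed mediated share and effect size.

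**Conclusion.** The point holds for post-intervention physical activity. Sections 2.2, 2.6.3 and 2.7, read together, permit conditioning on a variable that assignment to MT or SHD + MT can change, and such a model does not estimate the total effect stated in the aim. The 10% rule tends to keep that variable when it is a strong mediator. For post-intervention medication and clinical status the concern is possible only.

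The size of the bias cannot be derived from the document. If 25% to 50% of an effect ran through activity, adjustment would remove about 25% to 50% of it; with the assumed common cause acting in the same direction on activity and outcome, about 28% to 59%. These are illustrations under a linear model, not estimates for this trial.

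**What to change.** 1. In section 2.6.3, delete the reference to control after the intervention as far as adjustment is concerned. Both time points can stay as a description of when the data were collected.
2. In section 2.7, state that models for intervention effects use baseline covariate values only, including baseline accelerometry.
3. Apply the 10% change-in-estimate rule to baseline covariates only.
4. Report post-intervention activity and medication descriptively by arm, or in a mediation analysis labelled exploratory.

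The cost is a phrase in section 2.6.3 and a matching sentence or two in section 2.7. The baseline data are already part of the plan, no new data are needed, and the planned sample size does not change. Section 2.7 describes the analyses as still to be done.

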### 2.7. Statistical Analyses

Descriptive results will be expressed as median and inter-quartile range (IQR) or mean and standard deviation (SD), as appropriate, for continuous variables. Discrete variables will be presented as counts and percentages. The minimum threshold value for statistical significance used will be *p* ≤ 0.05.

The normality tests, histogram, and plot distribution will assess the normality of data distribution. Comparative analyses between participants and dropouts will be realised by *t*-test or Mann–Whitney U-test for continuous variables and Pearson-Chi Squared or Fisher exact test for categorical variables to determine whether attrition bias was observed. 

Potential differences among intervention groups in baseline measurements will be evaluated using a one-way Analysis of Variance (ANOVA) or correspondent non-parametric Kruskal-Wallis test. A Pearson Chi-squared or Fisher exact test will be used for between-group comparisons of categorical variables. 

Covariates (e.g., sociodemographic and economic characteristics; clinical history, such as the presence of comorbidities; and daily physical activity) were selected a priori and tested. The confounding variables will be entered as covariates in the ANOVA models. For each model, the contribution of all covariates will be tested separately; only the ones that change the magnitude of the association by at least 10% will be included in the final models. The fit of the models will be determined. Whenever necessary, we will use weighted samples to tackle the bias imposed by differential sampling probabilities.

A delta percentage will be calculated to assess the percentage of change between baseline and post-intervention assessments. An ANOVA or correspondent non-parametric test with repeated measures will be performed for differences in main effects and interactions for each dependent variable. When significant interactions are found, Bonferroni posthoc tests will determine the origin of the differences. Multivariable regression analyses will explore the associations between blood-based markers and metabolomics and the secondary outcomes.

Geographical information systems data will be collected. The associations of the primary and secondary outcomes with environmental features will be explored through generalised linear models to understand whether built environment food and PA features lead to statistically significant differences in participants’ dietary and exercise routines.

Multivariate analyses will be applied to discriminate between the metabolic profiles of the intervention groups, enabling the identification of the most relevant panel of spectral peaks differing between them [55]. Then, univariate statistical analyses, including hypothesis testing (ANOVA or the corresponding non-parametric test), effect size, and the area under the curve (AUC) obtained by receiver operating characteristic (ROC) analyses will be applied to test the statistical relevance of the panel of spectral peaks [55]. The metabolite annotation in NMR data will be performed. A comparison with the NMR spectral profiles of standard compounds presented in databases and the validation in 2D spectra (heteronuclear single-quantum coherence (HSQC) and total correlation spectroscopy (TOCSY)) acquired for one representative sample will be completed. In addition, the metabolic pathways altered in the groups under study will be interpreted through metabolomic pathway analyses [56].

All statistical analyses performed using the SPSS IBM Statistical Software version 25.0 (SPSS, Inc., Chicago, IL, USA) for macOS (Apple Inc., Cupertino, CA, USA) will be used for data assembly and graphical analyses.

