## Abstract

Data concerning the combined effect of diet and exercise interventions on overall health in the elderly are scarce. The MED-E project’s primary aim is to assess the effect of the different 3-month sustainable healthy diet (SHD) and multicomponent training (MT) interventions on several health outcomes in the elderly. A quasi-experimental study assigned older adults into four groups: (1) SHD, (2) MT, (3) SHD + MT, or (4) control group (CG). The SHD intervention included a weekly offer of a mixed food supply and individual and group nutritional sessions on the principles of an SHD. The MT groups were submitted to 50-min exercise sessions three times a week. The primary outcomes were blood biomarkers and metabolic profile alterations that were assessed pre- and post-intervention. Additionally, data on dietary intake and nutritional adequacy, physical fitness, body composition and anthropometry, cognitive function, quality of life, and geographical data were assessed at the same time points. The MED-E project’s study protocol and future results will add to knowledge about the importance and beneficial contribution of combined SHD and MT interventions on healthy ageing policies.

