### 2.3. Sample Size Estimation

The sample size was estimated based on previous literature and the ANCOVA to analyse the differences between and within groups [40]. A sample size calculation was conducted using G*Power 3.1.3 (Universität Düsseldorf, Düsseldorf, Germany) [41]. We predicted the inclusion of 25 participants per group, a total of at least 100 community-dwelling older adults, both men and women, considering a moderate effect size of 0.40, an alpha-risk of 0.05, and a beta-risk of 0.20 in a 2-sided test, and anticipating a 20% dropout rate.

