#### 2.5.4. Control Group (CG)

The CG received advice on following habitual dietary and PA routines. During the project intervention period, one nutrition session regarding the main principles of a healthy diet and two low-intensity PA sessions were offered to the participants in this group. Weekly telephone contact was conducted to ensure participant retention in the study.

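### The attrition check compares all participants with all dropouts by significance tests and does not mention arm, so it says little about dropout that differs between arms

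*Protocol article*

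**What the plan says.** Section 2.7 (Statistical Analyses) fixes three things about attrition.

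- The contrast: "Comparative analyses between participants and dropouts will be realised by" a t-test or Mann-Whitney test for continuous variables.
- The tests for categorical variables and the purpose: "Pearson-Chi Squared or Fisher exact test for categorical variables to determine whether attrition bias was observed". The variables are not listed.
- The threshold, set for all analyses in the section: "The minimum threshold value for statistical significance used will be" p ≤ 0.05.

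The following paragraph of section 2.7 does name the intervention groups, but only for comparing baseline measurements.

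Other sections bear on the point:

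- The Abstract says that the study "assigned older adults into four groups". The Discussion explains that the pandemic prevented randomisation.
- Section 2.3 plans "25 participants per group, a total of at least 100 community-dwelling older adults", "anticipating a 20% dropout rate". No dropout figure is given per arm.
- Section 2.5.2 removes from the final analyses anyone who misses more than 12 exercise sessions in a row.
- Section 2.5.4 says of the control arm: "Weekly telephone contact was conducted to ensure participant retention in the study".

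**The concern.** Attrition distorts a comparison of four arms when the number or the kind of people lost differs between arms. A two-group comparison of everyone who stayed with everyone who left does not look at arm. If frailer people leave one arm and fitter people leave another, the differences can cancel in the pooled comparison.

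The design makes arm-specific loss plausible. Two arms ask for three exercise sessions a week. Two arms receive food weekly, and the control arm has weekly retention calls. The missed-session exclusion can act only in MT and SHD + MT, because only those arms have sessions to miss. Section 2.7 does not say whether people removed under that rule count as dropouts in the attrition check. Without randomisation there is also no guaranteed starting balance.

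At stake is how far readers can trust a completer comparison of the primary biomarkers. A non-significant result could be taken as reassurance that the test cannot give.

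**Working it through.** **The plan's own figure.** Inputs from section 2.3: effect size 0.40 (read as Cohen's f), alpha 0.05, power 0.80, four groups, 20% dropout. A noncentral F calculation with 3 numerator degrees of freedom gives N = 73, or 76 when balanced (19 per group). Inflating, 19 / 0.8 = 23.75, so 24 per group against the stated 25. The plan's figure is reproduced to within rounding up. It follows that 100 × 0.20 = 20 dropouts and 80 completers are expected, or 5 and 20 per arm if losses are equal (the equal split is an assumption).

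**Power of the pooled t-test, 80 against 20.** The noncentrality is d / √(1/80 + 1/20) = d / 0.25 = 4d, with 98 degrees of freedom and a two-sided critical value of 1.984.

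| True difference d (SD) | Noncentrality | Power |
|---|---|---|
| 0.3 | 1.20 | 22% |
| 0.4 | 1.60 | 35% |
| 0.5 | 2.00 | 51% |
| 0.71 | 2.84 | 80% |

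**Opposite selection by arm (assumed).** Five of 25 leave each arm. Dropouts differ from completers by +k SD at baseline in the two exercise arms and by −k SD in the other two.

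- The pooled difference is (k + k − k − k) / 4 = 0, so the pooled test has nothing to find. By simulation it rejects about 4% of the time at k = 0.8 and about 4.5% at k = 0.5, no more than the nominal 5%.
- Within an arm, completers differ from everyone assigned by 0.20 × k. Between an exercise and a non-exercise arm the completers' baseline contrast therefore moves by 2 × 0.20 × k: 0.32 SD at k = 0.8 and 0.20 SD at k = 0.5.

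**Selection in one arm only (assumed).** With a 1 SD difference in a single arm, the pooled test rejects in 16% of runs.

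**From a baseline shift to bias in change.** Section 2.7 analyses pre-to-post change. Suppose dropout depends on the baseline value, and baseline and follow-up have equal SD and correlation r (not given in the documents). Expected change then has slope −(1 − r) on baseline, so the bias in the change contrast is (1 − r) × 0.32 in size:

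- r = 0.5: 0.16 SD
- r = 0.7: 0.10 SD
- r = 0.8: 0.06 SD

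Simulation gave 0.17 SD at r = 0.5 and 0.07 SD at r = 0.8, in line with the formula. With adjustment for the baseline value the bias is about zero. These figures cover selection on baseline only. If dropouts would also have changed differently by arm, the bias can be larger, and no comparison of baseline values can measure that directly.

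**Unequal rates (assumed).** Losses of 8, 8, 2 and 2 still total 20. Against an expected 5 dropouts and 20 completers per arm, chi-squared = 4 × 9/5 + 4 × 9/20 = 7.2 + 1.8 = 9.0 on 3 degrees of freedom, p = 0.029. A dropout-by-arm table shows this. A pooled comparison of baseline characteristics does not examine it.

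**Would testing within each arm help?** For 20 against 5 the noncentrality is d / √(1/20 + 1/5) = 2d. Power is 16% at 0.5 SD and 48% at 1 SD. More tests are not the remedy.

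**The case against.** The strongest case on the other side has five parts.

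- **The size of the harm.** A reader might infer that the primary biomarker contrasts are biased by 0.32 SD. The documents do not support that. The figure is a shift in a baseline variable among completers, and most of it cancels in an analysis of change or with baseline adjustment. The illustration also assumes exactly opposite selection, which makes the pooled test fail by construction. This stands, and the size is stated accordingly.
- **The decision rule.** A reader might infer that a non-significant result lets the trial declare attrition bias absent. Section 2.7 gives the purpose of the tests but ties no action to their result. This stands. What remains is that the tests are named as the means of deciding.
- **Pooling.** The text does not say that arms are pooled, and arm could be one of the unlisted categorical variables. The stated test would then compare dropout rates by arm. It would still not show different kinds of people leaving different arms.
- **Other safeguards.** It would be wrong to call this check the only handling of withdrawals. Section 2.3 inflates the sample, section 2.5.2 has the exclusion rule, and section 2.7 compares baseline across groups, adjusts for covariates and allows weighting. The weighting is for unequal sampling chances and is not linked to dropout. The baseline comparison, if run on analysed participants (the text does not say), flags the 0.8 SD illustration in about 19% of simulations. That is some warning, but weak.
- **Level of detail.** By-arm tables and imputation are often left to an analysis plan. Their absence alone would be no finding. The point is that the article has already chosen a contrast, tests and a purpose that do not fit each other.

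**Conclusion.** The point holds in limited form. The check in section 2.7 cannot do what it is said to do. It does not look at arm on its plain reading, and with about 20 dropouts a non-significant result is weak evidence at 0.3 to 0.5 SD (power 22% to 51%).

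The documents do not show that the primary results will be biased. Under the assumed opposite selection of 0.8 SD, the effect on the change contrast is about 0.06 to 0.17 SD, and near zero with baseline adjustment. It would be larger only if dropouts would also have changed differently by arm.

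The conclusion rests on pooling as the plain reading of a two-sample comparison, on equal losses of 5 per arm, and on assumed selection sizes and pre-post correlations. Severity is minor to moderate, because this is a diagnostic and not the primary model. The missed-session exclusion, which acts only in the exercise arms, and the lack of randomisation make it worth correcting.

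**What to change.** In section 2.7, replace the participants-against-dropouts significance check with:

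1. Numbers of dropouts and of section 2.5.2 exclusions, shown separately with reasons, by arm and counted from group assignment.
2. Baseline values of completers and dropouts by arm, with differences and confidence intervals, and no significance verdict on attrition bias.
3. One sensitivity analysis of the primary biomarkers that keeps everyone assigned, by multiple imputation or completion weights using arm and baseline variables (for example the baseline biomarker, age, sex, fitness and MNA-SF). Report it beside the completer analysis whatever items 1 and 2 show.

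Item 3 corrects only for losses explained by the variables used, and the report should say so. The baseline data needed are already part of the planned assessments. The cost is a change of wording, a little more analysis and slightly wider intervals.

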## 2. Design and Methods

The study was designed as a quasi-experimental, 12-week, four-armed, diet and exercise intervention with community-dwelling elderly residents from Porto, Portugal (Figure 1). This protocol report follows the Standard Protocol Items: Recommendations for Interventional Studies (SPIRIT) 2013 checklist [32]. 

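### Outcomes that fail a normality check move to a non-parametric route for which no covariate adjustment is described, in a study that was not randomised

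*Protocol article*

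**What the plan says.** Section 2.7 (Statistical Analyses) gives the main comparison: "An ANOVA or correspondent non-parametric test with repeated measures will be performed for differences in main effects and interactions for each dependent variable". Normality is to be judged by tests and plots. If an interaction is significant, Bonferroni post-hoc comparisons follow. Confounders enter as covariates in the ANOVA models and stay only if they change the association by at least 10%. Weighting is allowed where necessary, for unequal sampling probabilities. Neither 2.6.3 (Confounders) nor 2.7 names the baseline value of the outcome as a covariate. On relative change, 2.7 says: "A delta percentage will be calculated to assess the percentage of change between baseline and post-intervention assessments".

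Section 2.3 (Sample Size Estimation) states: "The sample size was estimated based on previous literature and the ANCOVA to analyse the differences between and within groups". Its inputs are given as "considering a moderate effect size of 0.40, an alpha-risk of 0.05, and a beta-risk of 0.20 in a 2-sided test", with "anticipating a 20% dropout rate", leading to 25 per group and at least 100 in total.

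The design is described as "quasi-experimental, 12-week, four-armed, diet and exercise intervention". On timing, 2.2 says: "Participants were assessed at baseline and after 3 months of intervention". The Discussions section explains that the pandemic prevented randomisation and warns that differences in baseline characteristics may distort the reading of the primary outcomes. Section 2.6.1 lists hs-CRP, insulin and triglycerides among the primary biomarkers.

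**The concern.** Without randomisation, covariate adjustment is the main protection against confounding that the plan describes. Section 2.7 attaches that protection to one of two analysis routes. An analyst who follows the text literally would adjust a biomarker that looks normal and run an unadjusted rank test on one that does not. Two primary outcomes from the same participants would then carry different degrees of confounding control, for a reason unrelated to confounding. The skewed markers, which include the inflammatory and insulin measures, would be the ones left unprotected.

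A lesser issue is that the sample size rests on a model called ANCOVA while the named test is a repeated-measures interaction. If the ANCOVA behind the sample size was one with the baseline outcome as covariate, the planned test is a different model with a different power.

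**Working it through.** **1. What each route can do.** The sentence in 2.7 promises main effects and interactions. The table shows what the usual tests deliver with two time points and four groups.

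| Test | Tests group-by-time? | Takes covariates? |
|---|---|---|
| Repeated-measures ANOVA with covariates | Yes | Yes |
| Friedman | No, within-subject time effect only | No |
| Wilcoxon signed-rank, within group | No, time effect only | No |
| Kruskal-Wallis on change scores | Group difference in change | No |

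None of the standard rank tests combines the promised interaction with the planned covariates. Weighting does not fill the gap, because 2.7 offers it for sampling probabilities and not for confounding.

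**2. How likely the switch is.** The document gives no distributions. I assume that hs-CRP, insulin and triglycerides are right-skewed, as they commonly are. On that assumption the route would be used for primary outcomes.

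**3. The plan's own sample size.** I used the noncentral F test with λ = f²N, numerator df = 3, denominator df = N − 4 − covariates, f = 0.40, alpha 0.05 and power 0.80. This gives N = 73, or 76 when balanced (19 per group). With 20% dropout, 19/0.8 = 23.75, so 24 per group and 96 in total. The stated 25 per group and 100 in total agree after rounding up. After 20% dropout, 100 leaves 80 evaluable.

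**4. Interaction test against baseline-adjusted ANCOVA.** With two time points the group-by-time test is a one-way ANOVA on change. For outcome SD s and baseline-post correlation ρ, the residual variances are 2s²(1 − ρ) for change and s²(1 − ρ²) for ANCOVA. Their ratio is 2/(1 + ρ): 1.33 at ρ = 0.5 and 1.18 at ρ = 0.7. The document gives no ρ and does not say to which SD f = 0.40 refers, so both readings are shown for 80 evaluable participants.

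- Reading A, f on the ANCOVA residual SD: f for change is 0.40·√((1 + ρ)/2), which is 0.346 at ρ = 0.5.
- Reading B, f on the raw outcome SD: f for change is 0.40/√(2(1 − ρ)), and f for ANCOVA is 0.40/√(1 − ρ²).

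| ρ (assumed) | A: ANCOVA | A: change | B: ANCOVA | B: change |
|---|---|---|---|---|
| 0.3 | 84.5% | 64.8% | 88.0% | 69.4% |
| 0.5 | 84.5% | 71.8% | 93.7% | 84.5% |
| 0.7 | 84.5% | 77.6% | 99.1% | 97.7% |
| 0.8 | 84.5% | 80.2% | 99.9% | 99.9% |

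These figures assume groups with comparable baselines.

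**5. Unequal baselines.** I simulated four arms of 20 with no intervention effect, one arm starting 0.5 SD higher and keeping that difference. Baseline-adjusted ANCOVA rejected in about 13% of runs at ρ = 0.5 and 9% at ρ = 0.7. The change score stayed near 5%. If the baseline difference instead regressed to the mean, the change score could be the biased one.

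**The case against.** The strongest reply is that 2.7 does not name the non-parametric test. A condensed article may leave the exact rank procedure, the transformation and the normality trigger to a fuller plan, and that plan might specify a rank method that takes covariates. This stands in part: the loss of adjustment is the consequence of using standard tests and is not stated outright. But the article itself fixes the switch and names the ANOVA models as the place where covariates enter, so the gap lies in what it says.

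Three stronger readings are tempting, and the document does not support them.

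- *The trial is underpowered because the wrong model is used.* An ANOVA with covariates is in form an ANCOVA. Section 2.3 does not say that its covariate is the baseline outcome, and the covariate list in 2.7 is given only as examples. The mismatch is therefore partly terminology. Under reading A with ρ of about 0.8 or more, or reading B with ρ of 0.5 or more, power stays at or above 80%.
- *Baseline-adjusted ANCOVA is plainly the right main analysis.* That holds under randomisation. With non-randomised groups that differ at baseline, ANCOVA and change score answer different questions, and step 5 shows that ANCOVA can mislead.
- *Percentage change is a tested endpoint.* The text says only that it will be calculated and attaches no test to it.

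**Conclusion.** The point holds for the non-parametric route. As written, adjustment for confounding is tied to the ANOVA models, and standard rank tests would remove it for skewed outcomes. Friedman would also fail to test the interaction that the sentence promises. This rests on two assumptions: that some primary biomarkers fail the normality check, and that a standard rank test is then used. The bias cannot be quantified, because the document reports neither group imbalance nor confounder effects.

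The difference between the sample-size model and the test model needs clarification and is not a demonstrated error. If f = 0.40 is on the ANCOVA residual SD, the change-score test loses about 7 points of power at ρ = 0.7 (84.5 − 77.6) and about 20 at ρ = 0.3 (84.5 − 64.8). Under other equally admissible readings it keeps at least 80%.

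**What to change.** - Replace the non-parametric switch in 2.7 with one covariate-adjusted model for every continuous outcome, using the same confounders throughout.
- Log-transform skewed biomarkers and judge normality on model residuals. If residuals remain poor, use robust or bootstrap standard errors, or a rank model that takes the same covariates.
- Report adjusted mean differences, or ratios for logged outcomes, with 95% confidence intervals. Keep percentage change as description.
- State which model is primary: post-intervention value adjusted for the baseline outcome, or change score. Report the other as a sensitivity analysis and say that neither is automatically unbiased when groups differ at baseline.
- In 2.3, state the covariate, the assumed baseline-post correlation and the SD to which f = 0.40 refers.

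The cost is wording in the analysis plan plus one sensitivity analysis. The outcomes and confounders are already part of the planned assessments, and no further data are needed. Section 2.6.1 describes the biomarker analyses as still to come, so according to the article the change can be made before results are known.
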